## Abstract

**Abstract:**

**Trial Registration:**

NCT01497782

## Background

### Virtual reality simulation

For virtual reality (VR) simulation the benefits are clear; the drawbacks are less clear. Throughout the last decade several studies have found positive effects of VR training on the learning curve as well as the improvement of basic psychomotor skills in the operating room, both in surgery and gynecology [1-4]. VR simulators offer standardized and reproducible laparoscopic tasks, ranging from simple basic skills training to complex procedures such as a cholecystectomy or salpingectomy. Despite the well-established advantages of VR simulators, the majority of surgical and gynecological departments encounter hurdles implementing this form of training in surgical education [5]. This is mainly due to lack of knowledge concerning the time, human resources, and costs needed to train novice surgeons to an adequate level [5-7].

Current literature suggests a predefined proficiency level based on experts' performance as a preferred outcome for novice training rather than a fixed training time [8-10], but it has not been investigated whether instructor feedback impacts training to this predefined proficiency level in complex operational tasks. One study suggested that proctored instruction did not offer any advantages to trainees compared with an independent approach [11]; however, the authors investigated only training of simple basic skills, such as instrument coordination, and did not include complex tasks, which is necessary in an advanced surgical training program.

### Self-directed learning

Researchers in motor skills have demonstrated that participants who self-direct their access to instruction or feedback during practice learn more than those whose access is externally controlled [12,13]. It is uncertain whether these results apply in a surgical training environment. One study found self-directed learning beneficial in terms of unlimited access to video instruction, the technical task being simple suturing of a wound [14]. The present randomized trial focuses on self-directed learning in regards to when to receive instructor feedback.

### Research goals

With a worldwide proliferation of simulation centers, it is essential to explore the optimal setting for laparoscopic training and investigate different learning approaches, e.g., a self-directed approach. The overall research goal of the present trial is to compare a feedback guided approach with an independent approach when training operational procedures on a laparoscopic VR simulator. Secondary research goals are to examine self-directed learning towards receiving instructor feedback along with potential sex differences and computer game experience during VR training. With this randomized trial we aim to study the need for human resources and optimal training methods when using VR simulation, and, thus, explore the best set up for surgical education.

We hypothesize that instructor feedback is pivotal when training on a VR simulator and will significantly improve surgical skills and self-perception. Additionally, retention of acquired surgical VR skills will be examined after six months.

## Methods/Design

### Participants

Participants are medical students recruited through advertisements on websites at three student associations (Young Surgeons, Young Anesthesiologist, and the General Student newspaper) at the Copenhagen University Medical School, Copenhagen, Denmark. All volunteers are then invited to an obligatory introduction meeting in order to qualify for the trial.Inclusion *criteria are*: 1) Medical bachelor degree (completion of the first 3 years out of six at University of Copenhagen Medical School). 2) Informed consent before enrollment. *Exclusion criteria are*: 1) having conducted more than 3 independent laparoscopic procedures. 2) Prior experience with VR simulation. 3) Not fluent in the Danish language.

### The VR simulator task and equipment

The VR simulator used is a LapSim^®^, version 2010, produced by Surgical Science, Sweden. Monitor: Dell 22", Simball™ 4D Joystick by G-coder Systems AB with a double footswitch.

All participants will be instructed in the operational technique and use of the VR simulator. The procedure specific VR task is a right-side laparoscopic salpingectomy due to an ectopic pregnancy. At the end of each completed task, the VR simulator sums up a weighted total score based on the values of 11 variables, which reflect time spent and quality of performance and presents an automated feedback on each variable, Table 1. This is available for all participants.

**Table 1 T1:** The 11 variables that generate the automated feedback on the VR simulator

Variable	Passing range
Total Time	> 280 (s)

Blood Loss	> 180 (ml)

Pool Volume	> 10 (ml)

Ovary Diathermy Damage	> 3 (s)

Tube Cut: Uterus Distance	> 4 (mm)

Bleeding Vessel Cut	0

Evacuation from Body	> 1

Left Instrument Path Length	> 2 (m)

Left Instrument Angular Path	> 350 (degrees)

Right Instrument Path Length	> 3 (m)

Right Instrument Angular Path	> 450 (degrees)

The training sessions are repeated until the predefined proficiency level, referred to as the 'expert level', has been reached twice within five consecutive repetitions. The instructor observes correct use of instruments and operation technique. The predefined proficiency level was set and validated in a previous study by the same research group [15], and it has shown to improve surgical skills, such as time and precision, in the operation room [4].

### The experimental intervention group and the control group

*The experimental intervention group *has the option of receiving three feedback sessions from an instructor. The instructor feedback consists of 10 to 12 min of standardized assessment of an operation on the VR simulator and assessment of the automated feedback produced by the VR simulator. The first feedback is given following the first operation on the VR simulator. The participants decide when they want the optional second and third feedback session. One instructor (the main author) provides the feedback in order to ensure consistency and uses the same template for every participant.

*The control group *only receives the automated feedback produced by the VR simulator.

Both groups are asked to complete a questionnaire before and after the trial pertaining to perception of own surgical skills, satisfaction with VR training, and carrier choice.

### Outcome measures

Primary outcome measures are number of repetitions to reach 'expert level' and total time (min) used to reach 'expert level'.

The secondary outcome measure is the weighted total score obtained when 'expert level' is reached which is based on the above mentioned 11 variables, Table 1.

Post hoc analyses will focus on results from the questionnaire reflecting the student's self-perception and the effect of sex and computer gaming skills.

### Ethics

The trial fully complies with the Helsinki Declaration on biomedical research. The Danish National Committee on Biomedical Research Ethics evaluated and approved the trial (journal number: H-3-2010-082). The Danish Data Protection Agency approved collection, analysis and storage of data, approval code 2007-58-0015/30-0996.

All participants are provided with written information on the trial. Participation is voluntary; no material goods are given to participants. The trial is registered at clinicaltrials.gov with trial registration number: NCT01497782.

### Randomization and participation

The central computerized randomization is performed by the Copenhagen Trial Unit. The randomization procedure is concealed and executed by using the participants' unique Central Personal Register number. The trial follows the CONSORT Statement for randomized trials, Figure 1. Stratification variables are sex and computer gaming experience (less than or equal to or more than 20 h annually).

### Sample size calculation and statistical analysis

Based on data in a previous study [15], we assume that participants in the intervention group and in the control group on the average will use 25 and 40 repetitions, respectively, to reach 'expert level'. With alpha set at 0.05 and beta set at 0.80, the sample size adds up to 98 participants in the trial.

The data will be analyzed using SPSS (Chicago, IL) version 15.0 and the SAS version 9.1. Two sided significance tests will be used.

*Analysis of the first experiment, i.e. instructor feedback approach vs. an independent approach: *The distributions of each outcome measure will be compared between the intervention group and the control group using the general linear uni-variate model and the analyses repeated with the co-variate semester number and the two protocol specified co-factors (indicator of sex, and indicator of computer game experience) included. A post hoc analysis including sex, the intervention indicator(I) and the interaction between I and sex will be conducted to explore the role of the sex.

If the assumptions of the general linear model (normally distributed residuals and variance homogenecity of the groups compared) cannot be fulfilled using simple transformations of the data, the distributions of the intervention group and the control group will be compared using a non-parametric test (Mann-Whitney) as will the two distributions of the results of the questionnaire reflecting the students self-perception at the end of the trial.

To adjust the P values for multiplicity Holm's procedure will be used [16].

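### Self-perception is recorded before and after training, but the planned comparison uses only end-of-trial answers; the test is valid but gives up precision, and the post hoc label conflicts with the hypothesis

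*Protocol article*

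**What the plan says.** Four statements in the protocol article bear on this point.

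- *Research goals* names self-perception beside surgical skills in the hypothesis: instructor feedback "will significantly improve surgical skills and self-perception".
- *The experimental intervention group and the control group* sets the measurement: "Both groups are asked to complete a questionnaire before and after the trial pertaining to perception of own surgical skills". The same questionnaire also covers satisfaction with the training and choice of career.
- *Outcome measures* lists repetitions and total time as primary and the weighted simulator score as secondary. Self-perception is in neither list: "Post hoc analyses will focus on results from the questionnaire reflecting the student's self-perception".
- *Sample size calculation and statistical analysis* gives the test. After naming Mann-Whitney as the fallback for the linear model, it adds: "as will the two distributions of the results of the questionnaire reflecting the students self-perception at the end of the trial".

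The same section describes the covariate adjustment, which belongs to the linear model: "the analyses repeated with the co-variate semester number and the two protocol specified co-factors". The two co-factors are sex and computer game experience, which are also the stratification variables under *Randomization and participation*. No analysis in the article uses the pre-trial questionnaire answer.

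**The concern.** A pre-treatment measurement of the outcome is often the best single predictor of its final value. Where it is collected and predicts the final score, leaving it out puts explainable variation into the error term. Any baseline difference that arises by chance also passes into the group comparison. A two-sample rank test cannot take covariates, so it cannot use the stratification variables either, although the protocol adjusts for them in its repeated linear-model analyses.

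A second, smaller matter is status. The effect is hypothesised in advance, measured by design and given a named test at a named time point, yet *Outcome measures* calls its analysis post hoc. A reader of the results could not tell whether a self-perception finding tests the stated hypothesis or is a by-product. Holm's procedure is planned without a list of the tests it covers, so the label also leaves open whether this P value belongs to the family.

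**Working it through.** **1. Is the baseline score used under any reading?** The Mann-Whitney sentence can be read in two ways. On the natural reading, Mann-Whitney is the planned test for the questionnaire, so no covariate enters. On the other reading, the questionnaire is first analysed by the linear model and Mann-Whitney is the fallback. Semester, sex and gaming experience would then enter the repeated analysis, but the pre-trial score would still be absent. The baseline is unused either way.

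**2. The plan's own figure.** No sample size or power is stated for self-perception. The total of 98 rests on repetitions (means 25 and 40, difference 15, alpha 0.05, and 0.80 read as power). No standard deviation is given, so it cannot be reproduced directly. Solving back with 49 per arm (1:1 allocation assumed):

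SD = 15 / [(1.960 + 0.842) × √(2/49)] = 15 / 0.566 ≈ 26.5.

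The 98 is used below only as a scale for the comparison.

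**3. Gain from adjustment in a linear analysis.** Let rho be the within-group correlation of baseline with final score. This is an assumption; the article gives no value.

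- Error variance with adjustment / without = 1 − rho²
- Equivalent unadjusted total = 98 / (1 − rho²)
- Power = Φ(0.566 × √(49/2) / √(1 − rho²) − 1.960), where 0.566 is the standardised difference giving 80% power unadjusted

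| rho (assumed) | 1 − rho² | Variance reduction | Equivalent N | Power, adjusted |
|---|---|---|---|---|
| 0 | 1.00 | 0% | 98 | 80% |
| 0.3 | 0.91 | 9% | 108 | 84% |
| 0.5 | 0.75 | 25% | 131 | 90% |
| 0.7 | 0.51 | 49% | 192 | 98% |

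**4. Comparison with Mann-Whitney itself.** The formula above compares two linear analyses, so the rank test was also simulated on normal data (49 per arm, standardised difference 0.566, 4,000 runs, two-sided 5%).

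| rho | Mann-Whitney, final score | ANCOVA with baseline |
|---|---|---|
| 0 | 78.4% | 79.9% |
| 0.3 | 77.8% | 83.5% |
| 0.5 | 76.8% | 88.8% |
| 0.7 | 77.6% | 97.1% |

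The gap of 1.5 points at rho 0 comes from using ranks on normal data and has nothing to do with the baseline.

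**5. Validity.** With no group difference (2,000 runs per value of rho), Mann-Whitney rejected in 4.3% to 5.0% of runs. ANCOVA rejected in 4.7% to 6.3%. The 6.3%, at rho 0.7, is Monte Carlo variation (standard error √(0.05 × 0.95 / 2000) ≈ 0.5 points), since the ANCOVA t-test is exact for the data simulated.

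**6. Chance imbalance.** The baseline difference between arms has standard error √(2/49) = 0.202 SD. A difference of that size shifts the unadjusted final comparison by rho × 0.202: 0, 0.06, 0.10 and 0.14 SD at rho 0, 0.3, 0.5 and 0.7.

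**The case against.** The best case for the plan is that nothing in it is invalid. Allocation is central and concealed, a comparison of final scores between randomised groups needs no baseline, and the test's error rate already allows for chance imbalance. A rank test is a defensible choice for questionnaire answers of unstated and possibly ordinal scale. All of this stands, and it limits the point to efficiency.

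Three further arguments stand in part.

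- *The gain may be small.* The eligibility criteria exclude students with prior VR simulation experience or more than three independent laparoscopic procedures. Self-ratings in such novices may cluster near the bottom of the scale and predict little. A reader might infer that students differ widely in self-rated skill at entry, and that the gain is therefore large. The document says neither, which is why rho 0 belongs in the range. Nor does the 1 − rho² formula carry over exactly to an ordinal model.
- *The two questionnaires may not be identical.* The article says one is completed before and after; it does not say that items and scoring match. Satisfaction with VR training could hardly be rated before any training. The point is therefore confined to self-perception items asked at both times.
- *The label may be only loose wording.* The article also calls a fully specified sex-by-intervention model post hoc, so the term seems to mean exploratory. A reader might infer that the questionnaire comparison will be devised after seeing the data. The statistical section rules that out by fixing its test and time point. The mismatch with the hypothesis is one of labelling, but it remains.

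It might also be said that an adjusted analysis may stand in a fuller plan. That does not remove the point, because the article itself fixes the time point and the test.

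**Conclusion.** The point holds as a loss of precision together with a labelling inconsistency. It is not an error of validity: a reader might infer that ignoring baseline biases the comparison, but randomisation and the simulated error rates show otherwise.

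The size cannot be fixed from the document. Against Mann-Whitney, under normal data and 49 per arm, ANCOVA gains about 6, 12 and 20 points of power at assumed rho 0.3, 0.5 and 0.7. At rho 0 the baseline contributes nothing. The larger figures should not be read as expected values. The consequence is moderate, because the outcome is not primary and the trial was not sized for it. The change is still worth making: the pre-trial answers are already collected, and a baseline covariate costs about one degree of freedom if it proves uninformative.

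**What to change.** In *Sample size calculation and statistical analysis*, state that for each self-perception item or score obtained at both times, the end-of-trial value is analysed with the pre-trial value, sex and gaming stratum as covariates. Use ANCOVA for a summed score, and proportional-odds regression or rank-based ANCOVA for ordinal items. Keep the Mann-Whitney test of final answers as a sensitivity analysis, and as the analysis for items with no meaningful baseline.

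In *Outcome measures*, list self-perception as a prespecified secondary or exploratory outcome in place of "Post hoc analyses will focus on results from the questionnaire", so that it agrees with the hypothesis, and say whether its P value falls within Holm's procedure.

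The cost is wording in the analysis plan. No new data, visits or participants are needed. The choice should be fixed before outcome data are examined.

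### The 98 participants are justified for repetitions alone at an unadjusted 0.05, but significance is judged after Holm adjustment over at least two primary outcomes, so the stated power for repetitions is not delivered

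*Protocol article*

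**What the plan says.** Protocol article, Outcome measures: "Primary outcome measures are number of repetitions to reach 'expert level' and total time (min) used to reach 'expert level". The two are listed side by side, with no ranking.

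Protocol article, Sample size calculation and statistical analysis: citing a previous study, the intervention and control groups "on the average will use 25 and 40 repetitions, respectively, to reach 'expert level". The size follows in one sentence: "With alpha set at 0.05 and beta set at 0.80, the sample size adds up to 98 participants in the trial". No standard deviation is given, and total time has no sizing assumption. The same section adds "Two sided significance tests will be used" and, at its end, "To adjust the P values for multiplicity Holm's procedure will be used [16". The tests that make up the Holm family are not listed.

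Protocol article, Missing values: the three sensitivity analyses are carried out only if the intervention effect is significant once multiplicity has been adjusted for. The adjusted result is therefore the one that counts.

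**The concern.** A sample size should be computed at the significance level at which the result will be judged. Here it is computed at 0.05 for one outcome, while two primary outcomes share that 0.05 through Holm. With two tests, Holm compares the smaller p-value with 0.025 and, only if that succeeds, the larger with 0.05. A repetitions result with p between 0.025 and 0.05 is then significant only if total time reaches p of 0.025 or less. The sizing sentence treats such a result as a success in every case.

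At stake is the chance of a positive finding on the one outcome the trial was sized for. A reader of the protocol would take that chance to be 80%.

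**Working it through.** **Inputs from the protocol article.** Difference 40 − 25 = 15 repetitions; two-sided alpha 0.05; total 98; two primary outcomes; Holm.

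**Assumptions.**
- Allocation is 1:1, so 49 per arm; the ratio is not stated.
- "beta set at 0.80" means power of 0.80. Taken literally it would be 20% power, which would need a standard deviation (SD) of about 66: 15 / [(1.960 − 0.842) × √(2/49)].
- 98 gives exactly 80% at 0.05. Without an SD, the figure of 98 cannot be reproduced independently.

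**Step 1: the SD that the plan's figure implies.** For two means, n per arm = 2 (z₁₋α/₂ + z_power)² SD² / difference². Solving for SD at n = 49:

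SD = 15 / [(1.960 + 0.842) × √(2/49)] = 15 / (2.802 × 0.2020) = 26.5, a standardised effect of 15/26.5 = 0.566. The t-test version gives an SD of 26.2 and 0.572.

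**Step 2: the first Holm step.** On this basis the expected test statistic is 2.802. The two-sided critical value at 0.025 is 2.241.

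Power = Φ(2.802 − 2.241) = Φ(0.560) = 71.2% (t-test 70.9%). At 0.05 it is Φ(2.802 − 1.960) = Φ(0.842) = 80.0%. Given the 80% anchor, the fall to 71.2% follows from the two alpha levels alone and needs no SD.

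**Step 3: full Holm over the two primary outcomes.** Repetitions is declared significant if p₁ ≤ 0.025, or if p₁ ≤ 0.05 and p₂ ≤ 0.025, where p₂ belongs to total time. So

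power = P(p₁ ≤ 0.025) + P(0.025 < p₁ ≤ 0.05 and p₂ ≤ 0.025).

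The first term is 71.2%. The second is at most 80.0 − 71.2 = 8.8 points, and is smaller whenever total time can miss 0.025. Simulation with bivariate normal test statistics (at least 1,000,000 draws per setting) gives:

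| Standardised effect on time, relative to repetitions | Correlation | Power, repetitions | Power, at least one outcome |
|---|---|---|---|
| none | 0 to 0.95 | 71-72% | 72-73% |
| 0.5 | 0.5 | 72.0% | 72.8% |
| 0.5 | 0.95 | 71.2% | 71.2% |
| 0.8 | 0.5 | 74.2% | 78.6% |
| 0.8 | 0.95 | 71.4% | 71.5% |
| equal | 0 | 77.5% | 91.7% |
| equal | 0.5 | 76.5% | 85.3% |
| equal | 0.8 | 75.6% | 79.9% |
| equal | 0.9 | 75.1% | 77.4% |
| equal | 0.95 | 74.6% | 75.5% |

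**Step 4: dependence on the missing SD.** If the true SD were 25, power for repetitions with 49 per arm would be 84.4% at 0.05 and 76.7% at 0.025. With an SD of 30 it would be 69.7% and 59.2%.

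**The case against.** **No stated number is shown to be wrong.** This stands. The SD is not in the article, and with a small enough SD the trial would exceed 80% even at 0.025 (SD 20: 92.9%). But 98 would then not be the size that gives 80% at 0.05, which is how the article justifies it. The finding concerns the mismatch between that justification and the decision rule, and its size is conditional.

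**Holm is not Bonferroni.** This also stands. The 71% is the lower bound, reached when total time shows little or no effect. Total time accumulates over the same repetitions, so some effect on it is plausible and the loss is then smaller. It does not disappear: the second term in Step 3 cannot reach its full 8.8 points while total time has any chance of missing 0.025.

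**A win on either outcome might be what matters.** The article does not define success as a win on repetitions. Where the time effect is no larger than that on repetitions, power for at least one win reaches 80% only if the effects are similar and, with equal effects, the correlation is about 0.8 or lower. The article does not define success as either-or, and its sizing sentence concerns repetitions. This softens the point without removing it.

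**Stronger readings that the document does not support.**
- A reader might infer that the secondary score, the covariate-adjusted repeats and the questionnaire all join the Holm family, pushing power down further. The article does not say so. It separates primary, secondary and post hoc outcomes, and a full analysis plan may list the family.
- A reader might add a loss for missing data because the analysis is complete case. No missing-data rate is given, and the calculation is not shown, so one cannot tell whether 98 already contains an allowance.
- A reader might see a threat to validity. Sizing on one outcome and adjusting over two is conservative for type I error; it costs power and causes no bias.

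**Conclusion.** The point holds in limited form. If 98 participants give 80% power for repetitions at two-sided 0.05, the same 98 give about 71-77% under the decision rule that the article sets. The lower bound is 71%, about 71-74% applies with a time effect half to 0.8 as large (correlation 0.5 to 0.95), and about 75-77% with an equal one. The loss is roughly 3 to 9 points, on the narrowest possible family of two tests.

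This rests on 1:1 allocation, on reading the stated beta as power, and on the 80% anchor in place of the missing SD. It is a moderate, correctable fault in the power statement and does not undermine the trial.

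**What to change.** - State that the Holm family for the confirmatory claim is the two primary outcomes, with one named analysis of each.
- Restate power for repetitions as about 71-77% under Holm, with 71% as the lower bound, and give the assumed SD behind it. Correct the beta wording in the same sentence.

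This changes wording only and needs no more participants. The cost is a less favourable stated power. For scale, keeping 80% at the first Holm step would need 98 × (2.241 + 0.842)² / (1.960 + 0.842)² = 118.7, so 120 participants in equal arms. That is the worst case for two tests, and the fix does not depend on it.

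Optional alternative: a fixed sequence, with repetitions tested first at 0.05 and total time at 0.05 only if repetitions is significant. This keeps type I error control and restores the planned power for repetitions. It is a change of confirmatory strategy: it ranks two outcomes now listed as equals, and it blocks any claim on total time if repetitions is not significant. It would have to be fixed before the outcome data are seen.
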